**RESEARCH PROPOSAL**

**1. THE NEED FOR A TRIAL**

**1.1 What is the problem to be addressed?**

Diarrhoeal disease is the second-leading cause of death for children under the age of five ([1](#_ENREF_1)). The majority of these deaths are in lower-income countries; mortality associated with gastroenteritis is rare in North America ([2](#_ENREF_2)). A recent major study including over five thousand children presenting to health centres in sub-Saharan Africa with moderate-to-severe diarrhoea documented an overall mortality of 3.2% ([3](#_ENREF_3)). Unfortunately, the impact of diarrhoea is not limited to mortality; gastroenteritis causes a staggering amount of morbidity as well. A multi-country analysis pooling data from nine large longitudinal studies in lower-income countries showed that both the cumulative diarrhoeal incidence (number of diarrhoeal episodes/year) and the longitudinal diarrhoea prevalence (proportion of days with diarrhoea) were both associated with stunting (height-for-age more than two standard deviations below the mean) ([4](#_ENREF_4)). With every five episodes of diarrhoea, a 13% increase in the odds of stunting at 2 years was observed; the proportion of stunting at age 2 attributable to 5+ diarrhoeal episodes was estimated at 25% ([4](#_ENREF_4)). Stunting, of course, is a critical measure of well-being, as height-for-age at 2 years has been shown to be the best predictor of human capital ([5](#_ENREF_5)). Enteric infections in infants and toddlers have also been associated with cognitive deficits, less attained schooling, less economic productivity, metabolic derangements, and, least surprisingly, lower adult height ([5-7](#_ENREF_5)).

Most episodes of diarrhoea in children are caused by enteric viral pathogens, which cannot be treated with antimicrobials; the essentials of management for patients with viral gastroenteritis are rehydration, zinc treatment, and correction of electrolyte imbalances([8](#_ENREF_8)). In an effort to prevent some of these episodes, rotavirus vaccine has been integrated into the universal vaccination programs of many lower-income countries within the past five years. However, acute gastroenteritis can also be caused by bacterial and protozoan pathogens, and these infections *can* be attenuated with prompt antimicrobial therapy. Though many of these infections will eventually spontaneously resolve ([9](#_ENREF_9)), it is the standard of care in Canada – where access to good medical care is free, where HIV and TB are very rare in children, and where severe malnutrition is essentially an anachronism – to treat enteric infections caused by *Shigella, Campylobacter,* and enterotoxigenic *E. coli* (ETEC) with antimicrobials. In sub-Saharan countries, where mortality from diarrhoea is orders of magnitude higher, it is only rational to recommend the same. There are no placebo-controlled randomized trials showing a mortality benefit from antimicrobial therapy for bacterial enteritis in lower-income countries, possibly due to the lack of clinical equipoise around this point, but a recent systematic review hypothesized that antimicrobial therapy leads to a 99% reduction in mortality from bacterial enteritis associated with bloody stools ([10](#_ENREF_10)). Much time and effort has been made into developing a vaccine against ETEC to prevent the mortality in young children presumed to be attributable to this pathogen ([11](#_ENREF_11)).

Unfortunately, clinicians in many parts of the world do not have ready access to rapid, reliable diagnostics that can provide a microbiologic (aetiologic) diagnosis for acute gastroenteritis. Consequently, cases of diarrhoea without blood are presumed to be viral, and current World Health Organization guidelines recommend against empiric antimicrobial therapy for cases of uncomplicated acute gastroenteritis([8](#_ENREF_8)). In contrast, if there is bloody stools (dysentery), the likelihood that the diarrhoea is caused by a treatable pathogen increases substantially; current WHO guidelines suggest empiric therapy for dysentery using antibacterials targeted against *Shigella* spp., widely assumed to be the most common severe cause of bacillary dysentery ([12](#_ENREF_12)). The problem with this approach is that in many regions the proportion of non-dysenteric diarrhoea caused by treatable bacteria and protozoa may be substantial. Our preliminary results show that in Gaborone, Botswana, in 2011, over 35% of over five hundred children admitted to hospital because of gastroenteritis – most of whom did not have dysentery – were found to be harbouring a treatable enteric pathogen using advanced molecular diagnostic techniques.

All agree that bacillary (or protozoan) dysentery should be treated with antibiotics – what about bacillary (or protozoan) gastroenteritis not accompanied by bloody stools? The Global Enteric Multi-Center study found that two of the pathogens most closely linked with deaths associated with acute gastroenteritis were ETEC and *Cryptosporidium*, neither of which cause dysentery ([13](#_ENREF_13)). It is the standard of care in North America to treat traveller’s diarrhoea (most commonly caused by ETEC) with antibiotics to reduce morbidity; a Cochrane review has provided the evidence base for this practice ([14](#_ENREF_14)). ETEC, of course, has been hypothesized to be the most common cause of bacterial enteritis in young children in lower-income countries and is likely to cause much more severe disease in this population compared to healthy adult travellers from high-income countries ([11](#_ENREF_11)). Even pathogens that can cause dysentery are often treated with antimicrobials when bloody stools are not present; in a randomized control trial (RCT) investigating optimal therapy for shigellosis in Israel, 40% of study participants did not have bloody diarrhoea ([15](#_ENREF_15)). A randomized placebo-controlled trial examining antibiotic therapy for campylobacteriosis in Croatia, where none of the 120 participants had severe dehydration (in contrast to patients typically hospitalized for acute gastroenteritis in Africa), included only 10 participants with visibly bloody stools. Despite the fact that few subjects had dysentery, azithromycin was shown to lead to significantly increased rates of clinical cure as compared to placebo, as well as significantly faster improvement ([16](#_ENREF_16)). Leading researchers in global child health have suggested that important health outcome improvements could be seen with even minor interventions targeted at treatable bacterial and protozoan enteric infections; the context for this statement was the observation of major reductions in all-cause mortality after five thousand Ethiopian children were given one dose of azithromycin in a mass treatment trial for trachoma, a large proportion of which presumably did not have acute severe dysentery at the time ([17](#_ENREF_17)). Overall, it would seem logical that children with proven infectious bacterial/protozoan diarrhoea would benefit from antimicrobial therapy regardless of whether they have blood in their stool.

To permit timely treatment of bacterial/protozoan gastroenteritis, rapid diagnosis is needed (empiric treatment of all children with gastroenteritis with antibacterials and antiparasitics would be ill-advised from both medical and economic standpoints). Unfortunately, standard microbiologic techniques for the diagnosis of bacterial enteritis are labour-intensive, cannot detect ETEC, and require special equipment for the detection of *Campylobacter*; they also take 2-3 days in highly resourced laboratories, to say nothing of typical laboratories in sub-Saharan Africa. Consequently, advanced diagnostics – molecular diagnostics or simple immunoassays – are needed. Once these diagnostics have been integrated into routine clinical care of young children in lower-income-country settings, rapid treatment will become possible, and the mortality and morbidity benefits can be directly measured. This evaluation will be critical in determining how many children’s lives will be saved, and how much child stunting can be prevented, by their integration into routine care.

Probiotic therapy – the administration of ‘good’ bacteria – also holds promise for the supportive treatment of children with infectious gastroenteritis. A Cochrane review pooled data from 63 studies of proven or presumed infectious acute diarrhoeal disease (n=8014) and found that probiotic treatment decreased duration of diarrhoea by a mean of 24.5 hours (95% CI 16-34 h) and reduced stool frequency on day 2 of illness by a mean of 0.8 stools (95% 0.5-1.1 stools) in infants and young children, though many different probiotic preparations were used ([18](#_ENREF_18)). Almost as importantly, no significant or serious adverse reactions were found in all of these children. The majority of these studies were done in children with viral gastroenteritis, and there is no substantial evidence supporting the use of probiotics in children with bacterial or protozoal enteritis; however, it must be noted that these studies did not use advanced molecular diagnostics, and so it is very possible that many of these children had unrecognized bacterial co-infections. Another Cochrane systematic review has demonstrated that probiotic therapies can prevent paediatric antibiotic-associated diarrhoea when administered concurrently with antibiotics, suggesting that concomitant administration of antibacterials will not necessarily render the probiotics inactive ([19](#_ENREF_19)). Overall, there is a rational basis for exploring the use of probiotics in the sub-Saharan context for the treatment of infectious enteritis, whether viral, bacterial or protozoan.

**1.2 What are the principal research questions to be addressed?**

Our research question is whether, in children under five years of age admitted to hospital because of acute non-dysenteric diarrhoeal disease, rapid testing of stools for treatable bacterial/parasitic pathogens – accompanied by prompt treatment of these pathogens if detected – plus treatment with *Lactobacillus GG***,** will lead to decreased mortality and stunting at 60 days. Testing this hypothesis will likely require a large multicentre randomized trial, so we propose to first conduct a **pilot** **whose goal will be to demonstrate feasibility**. The specific feasibility criteria of this pilot are:

1) to enroll at least 100 participants during the 12-month study period;

2) to ensure that >95% of participants have a rectal swab taken within 18 hours of admission;

3) to verify that >95% of rectal swabs in the experimental group are resulted within 48 hours of admission;

4) to ensure >95% of participants found to have a treatable enteric pathogen are prescribed appropriate antimicrobials;

5) to ensure that >95% of participants prescribed antimicrobials start them within 24 hours of the test being resulted;

6) to contact >95% of participants 7-14 days after discharge from hospital; and

7) to contact >90% of participants 60 days after admission to hospital.

All aspects of the proposed follow-up trial will be assessed, including enrolment, randomization, follow up, methods for outcome assessment, and event rates. The data collection forms and data management strategy will be tested, data to derive a precise sample size will be generated, and assumptions for a cost effectiveness analysis will be assessed.

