**2. THE PROPOSED TRIAL**

**2.1 What is the proposed trial design?**

A single-centre, randomized, factorial (2x2), controlled, pilot trial. Children aged 3-60 months admitted to the paediatric ward of the Princess Marina Hospital in Gaborone, Botswana, with acute non-dysenteric diarrhoeal disease will be randomized to one of four arms: rapid stool testing/targeted antimicrobial therapy plus probiotic treatment, rapid stool testing/targeted antimicrobial therapy plus placebo treatment, delayed stool testing plus probiotic treatment, or delayed stool testing plus placebo treatment. The primary outcome is 60-day mortality. See Appendix 1 for flowchart of study procedures.

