**2.3 What are the planned trial interventions?**

**2.3.1 All participants.** Data to generate Vesikari scores([20](#_ENREF_20)), a validated measure of gastroenteritis severity, will be collected at enrollment, and all study participants will be weighed and measured using calibrated apparatus. Percent dehydration will be abstracted from the paediatric team admission note (subjective dehydration) and will also be calculated comparing weight nadir in hospital to weight at discharge from hospital (objective dehydration). All participants will have a rectal flocked swab taken at enrollment within 18 hours of admission. Most of these children will not be started on antimicrobials at admission, as per current Princess Marina Hospital and World Health Organization standards, excepting children with severe acute malnutrition. Rehydration procedures will be decided by the attending physician; as per Princess Marina Hospital dehydration protocols, all those with severe dehydration receive intravenous rehydration with isotonic fluids and those with mild-moderate dehydration receive WHO-standard oral rehydration solution (ORS). It is standard of care at Princess Marina Hospital to also provide zinc treatment for gastroenteritis.

**2.3.2 Rapid testing and targeted antimicrobial therapy plus probiotic therapy arm.** These participants will be started on *Lactobacillus reuteri* within 24 hours of enrollment**.** All of these participants’ rectal swabs will be processed using our novel diagnostic techniques and resulted within 48 hours. It will be recommended to the attending physician that *Shigella,* ETEC, and *Campylobacter* infections be treated with azithromycin, and *Cryptosporidium* infections be treated with nitazoxanide. It will also be recommended that antimicrobials will be started as soon as possible, preferably on the day the test results become available, and antimicrobials will be provided free of charge. Probiotic therapy will be continued until the measurement of the primary outcome, 2 months post-enrollment.

**2.3.3 Rapid testing and targeted antimicrobial therapy plus placebo therapy arm.** These participants will be started on placebo therapy within 24 hours of enrollment and will have rectal swabs processed rapidly (see 2.3.2). Placebo therapy will be continued until the measurement of the primary outcome, 2 months post-enrollment.

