**2.11 What is the proposed sample size?**

For this pilot study, a sample of 100 participants will be adequate to evaluate the feasibility criteria.

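### The research question names one probiotic, both probiotic arms name another, and nothing in the protocol reconciles them

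*Protocol*

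**What the plan says.** Section 1.2 asks whether rapid stool testing with prompt targeted treatment, together with "Lactobacillus GG", "will lead to decreased mortality and stunting at 60 days". It then defers the definitive answer: "Testing this hypothesis will likely require a large multicentre randomized trial, so we propose to first conduct a" pilot directed at feasibility. The same section expects the pilot to examine event rates and to produce data for sizing the later trial.

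Section 2.1 sets out a 2x2 factorial design and describes the probiotic factor only in general terms, for example "rapid stool testing/targeted antimicrobial therapy plus probiotic treatment". It also states: "The primary outcome is 60-day mortality".

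Section 2.3 is where the product is specified. The rapid-testing probiotic arm (2.3.2) receives "Lactobacillus reuteri", and the delayed-testing probiotic arm names the same organism. The number 2.3.3 is used twice, and the delayed-testing probiotic arm is the second section to carry it. In both arms treatment starts within 24 hours of enrolment and runs to the two-month outcome assessment.

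The background in section 1.1 relies on a pooled review, "though many different probiotic preparations were used", and singles out neither agent.

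**The concern.** The probiotic is one of the two randomised factors, and young children take it for about two months. Section 2.16.1 says it is not standard of care in Botswana and argues its safety from probiotic use in general. A reader of the protocol should be able to tell which organism the hypothesis concerns and see that the arms deliver it. Here the two statements disagree.

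What is at stake is the link between hypothesis and data. The pilot is meant to inform a larger trial of the section 1.2 hypothesis. Event rates, adherence or growth data from the probiotic arms would describe the organism in section 2.3. If they were carried forward as planning values for the organism in section 1.2, the later trial would rest on figures from a different intervention. The pilot also has a formal clinical comparison of its own, since section 2.13 plans an intention-to-treat chi-square test on mortality. The mismatch therefore also affects how that result may be described.

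**Working it through.** The question is which intervention is meant, so the check is mainly a comparison of text. The only arithmetic is the number of children affected.

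**Every place that mentions the probiotic**

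| Protocol section | How the probiotic is named |
|---|---|
| 1.1 (background) | Generic; pooled evidence over mixed preparations |
| 1.2 (research question) | "Lactobacillus GG" |
| 2.1 (design) | Generic |
| 2.2.1 (inclusion criteria) | Generic |
| 2.3.2 (rapid testing plus probiotic) | "Lactobacillus reuteri" |
| Second 2.3.3 (delayed testing plus probiotic) | "Lactobacillus reuteri" |
| 2.13 and 2.14 (analysis, subgroups) | Generic |
| 2.16.1 (risks) | Generic |

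One name appears once, in the hypothesis. The other appears twice, once in each arm that receives the probiotic. All three are in the current body of the protocol. None is in an amendment log, a redacted passage or a broken table. No section records a change of product, designates a substitute or calls the two equivalent. The background cannot settle the matter because its evidence is not specific to either agent.

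**What depends on the mismatch**

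- Seven feasibility criteria (1.2, repeated in 2.10): these cover enrolment, swab timing, result timing, antimicrobial prescribing, antimicrobial start and two follow-up contacts. None involves the probiotic, so none is affected.
- Sample size (2.11): its only justification is that "a sample of 100 participants will be adequate to evaluate the feasibility criteria". Not affected.
- Rapid versus delayed testing: the definition of this factor does not depend on the probiotic. Not affected.
- Probiotic versus placebo: both probiotic arms name the same organism, so the randomised contrast is coherent for the product given. What fails is its correspondence to section 1.2.
- Planning data for the follow-on trial: affected for the probiotic factor only.

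**Number of children**

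Inputs: 100 participants (2.11), allocation 1:1:1:1 over four groups (2.5), two of which receive the probiotic.

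- Per group: 100 / 4 = 25.
- Assigned to probiotic: 2 × 25 = 50.

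Section 2.2.1 keeps children with severe acute malnutrition out of the probiotic/placebo randomisation. If m of the 100 are such children, the expected number assigned to probiotic is (100 − m) / 2. This is 50 when m = 0 and falls by one for every two such children enrolled. The protocol gives no value for m, so about 50 is an upper bound at a total of 100.

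**The case against.** The strongest reply is that section 2.3 is the operative text and is consistent. It names one organism, the same in both arms, and someone following it would meet no conflict. On this view the protocol has one stray name in a motivating paragraph. Much of this stands, and it rules out three stronger conclusions that a reader might draw.

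- *That one factor of the 2x2 design has no defined intervention.* The documents do not support this, because the arm descriptions agree with each other.
- *That the trial fails to test its own hypothesis.* Section 1.2 says that the hypothesis will probably need a large later trial and gives this pilot a feasibility goal. A mortality test is planned here, but the pilot is not presented as the definitive test.
- *That product supply and placebo matching are compromised.* The protocol describes neither the sourcing of the product nor the formulation of the placebo, so this would be inference.

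It is also fair to say that the analysis section needs no change, since its generic wording fits whichever product is named.

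The reply does not remove the contradiction. Section 1.2 is the formal statement of the research question, and nothing in the protocol ranks it below section 2.3 or the reverse. That one name appears twice does not show it to be the intended one. The feasibility argument also has a limit, because section 1.2 itself counts event rates and sample-size data among the pilot's products.

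**Conclusion.** Wrong as written: an internal inconsistency between the research question and the two probiotic-arm descriptions. Followed literally, the probiotic comparison and any planning inputs drawn from those arms would concern a different organism from the one in the hypothesis.

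The effect is confined to one of the two factors and to at most about 50 of 100 children. It does not threaten the internal validity of the probiotic-versus-placebo contrast for the product given.

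The conclusion assumes that the two names denote different products, which is their plain reading and which no text in the protocol contradicts. The count assumes a total of exactly 100 with equal allocation. It does not matter to the conclusion which of the two names was intended.

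**What to change.** Reconcile section 1.2 with section 2.3.2 and with the delayed-testing probiotic arm (the second section numbered 2.3.3), so that one product is named in all three places. The choice is for the sponsor, and this review takes no position on it. Correcting the duplicated number 2.3.3 in the same amendment would make the cross-reference unambiguous.

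The cost is a wording change in one place (section 1.2) or two (the arm descriptions), depending on the sponsor's decision. Design, sample size, feasibility criteria and planned analysis need no change.

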**1.3 Why is a pilot study necessary?**

This proposed pilot study is an essential first step prior to conducting an expensive multicentre trial. The process of the study must be verified; we will need to optimize communication between the study nurse and the microbiology laboratory to ensure that study specimens are obtained in a timely fashion, processed completely, and that results are communicated in an efficient manner back to the treating physicians. We will also need to ensure that a mechanism is put in place to ensure follow-up and that all outcomes can be reliably measured. We will likely need to compare various point-of-care assays to determine which will perform optimally in a clinical trial setting.

**1.4 How will the results of the trial be used?**

Before the widespread introduction of a new diagnostic test, there must be demonstrable benefit associated with its use; this is even more important in a setting such as sub-Saharan Africa where the public health care systems have very limited resources. Many organizations, both public and private, are spending time developing novel diagnostics – but no one has yet investigated their use in a systematic fashion within the parameters of a randomized controlled trial. The results of this trial will be of paramount importance to clinicians, patients, and health-care policy-makers in resource-limited settings.

